## Abstract

**Background:**

Breast cancer is the most frequently diagnosed cancer and the leading cause of cancer death in women. Approximately 50% of breast cancers are discovered at an early stage in patients for whom conservative surgery is indicated. Intraoperative localization of non-palpable breast lesions is generally accomplished using a hook wire to mark the area of concern under ultrasound or stereotactic localization. But this technique has several drawbacks (painful, stressful…). We propose the use of a wire-free breast lesion system using miniature radiofrequency identification (RFID) tags. This technique could improve patient comfort and surgical comfort for surgeons. We therefore propose a study to assess the interest of introducing the RFID localization technique at the Jean PERRIN comprehensive cancer center.

**Methods:**

This is a single-center prospective trial designed to assess the interest in introducing the RFID localization technique at the Jean Perrin center. It aims to show the superiority of the RFID technique in terms of patient tolerance compared to the gold-standard (hook wire). A sequential inclusion in time will be performed: 20 inclusions in the gold-standard group, then 20 patients in the RFID group before repeating the inclusion scheme. Any patient requiring preoperative localization will receive a senology consultation. The RFID tag will be placed during this consultation. The hook wire localization will be done the day before the surgery. Patients will fill out a Hospital Anxiety and Depression scale (HAD) questionnaire at the time of inclusion. They will then fill out a satisfaction questionnaire in 2 steps: during the placement of the device (RFID tag or hook wire) or during the postoperative consultation at 1 month. Radiologists and surgeons will fill out a questionnaire to evaluate the localization technique, respectively after the localization and surgery procedures.

**Discussion:**

The RFID study is the first study in France which specifically assesses the interest of the RFID localization in terms of patients comfort. Patient comfort is one of the key elements to take into consideration when managing patients in oncology and new technologies such as RFID tags could improve it.

**Trial registration:**

ClinicalTrials.gov ID; NCT04750889 registered on February 11, 2021.

**Supplementary Information:**

The online version contains supplementary material available at 10.1186/s12885-023-11190-w.

## Background

Breast cancer is the most frequently diagnosed cancer and the leading cause of cancer death in women with 58,500 new cases in France in 2018. Approximately 50% of breast cancers are discovered at an early stage in mainly young patients and for whom conservative surgery is indicated. Intraoperative localization of non-palpable breast lesions is generally accomplished using a hook wire to mark the area of concern under ultrasound or stereotactic localization.

However, this technique has several drawbacks. Indeed, it appears as a relatively painful and anxious procedure for patients. It can also be a source of difficulty for the surgeon, because only the entry point is visible: the orientation and length of the wire are assessed on a control image. Moreover, it leads to a time coordination obligation between radiologists and surgeons since the localization device cannot remain in place for more than 24 h. Finally, because the end of the hook wire comes out at one end of the breast and goes through the skin it can be associated with a risk of infection, breakage, accidental exposure to blood or wire dislodgement.

During the last decades, other localization techniques have been studied as alternatives to hook wire [1]. None of these alternatives has been able to prove its superiority compared to hook wire, which remains the gold-standard. A wire-free breast lesion system using miniature radiofrequency identification (RFID) tags appears as an interesting alternative (LOCalizer™ with CE marking and FDA labelling). It is a radio-opaque tag that emits a radiofrequency signal when excited at a specified wavelength. It is carried by a 12-gauge coaxial needle and can be positioned under ultrasound or stereotactic guidance. A receiver that registers the RFID number is available for radiologists and handheld reader displays the distance to the tag in millimeters (up to 6 cm) for surgeons. This technique aims to improve patient comfort and surgical comfort by increasing localization accuracy. Moreover, radiologists would no longer be dependent on the surgical schedule. The oblong shape of the tag should reduce the risk of accidental exposure to blood, and material breakage. Nevertheless, the cost of this technique remains significantly higher than the hook wire. Acceptance and changes in practices by radiologists and surgeons are necessary.

To date, few articles address radiofrequency localization, and most studies are of recent publication [2–5]. The main publications on radiofrequency localization deal with a small number of patients, without comparison to the gold-standard, and primarily assess safety, acceptance, and technique performance [2, 4, 6]. Only one American retrospective study implies a large number of patients (*n* = 503) and compares RFID localization qualities to the gold-standard [3]. They concluded that RFID tag localization is a possible alternative to hook wire and should be considered for non-palpable breast lesions. To date, no study has looked at the interest of the technique in terms of patient comfort. We therefore propose a study to assess the interest of introducing the RFID localization technique at the Jean Perrin comprehensive cancer center.

## Methods and study design

### Study objectives and outcomes

The primary objective of the RFID trial is to show the superiority of the RFID technique in terms of patient tolerance compared to the gold-standard (Table 1). It also aims to determine surgeons and radiologists perceptions of the RFID technique compared to gold-standard.

**Table 1 Tab1:** Primary and secondary objectives

**Primary objective**	• To show the RFID technique superiority in terms of patient tolerance compared to the gold-standard
**Secondary objectives**	• To compare the surgeon’s perception of the localization by RFID to the gold-standard
	• To compare the radiologist’s perception of the localization by RFID to the gold-standard
	• To demonstrate the non-inferiority of the RFID technique over the gold-standard in terms of performance

### Study design

This is a single-center prospective trial designed to assess the interest in introducing the RFID localization technique at the Jean PERRIN center. Study design is presented in Fig. 1.

**Fig. 1 Fig1:**
[figure not shown]
Design of the RFID study. The participation to the study will be proposed during a senology consultation to any patient requiring preoperative localization. The RFID tag and the hook wire will be respectively placed during the senology consultation and the day before the surgery. In the two groups, patients will fill out a Hospital Anxiety and Depression scale (HAD) questionnaire and then fill out a satisfaction questionnaire during the placement of the device (RFID tag or hook wire) and during the postoperative consultation at 1 month. Radiologists and surgeons will also fill out a questionnaire respectively after the localization and surgery procedures

Any patient requiring preoperative localization will receive a senology consultation and participation in the study could be proposed. A sequential inclusion in time will be performed: 20 inclusions in the gold-standard group, then 20 patients in the RFID group before repeating the inclusion scheme. Eighty patients will be enrolled.

The RFID tag or the hook wire will be respectively placed during the senology consultation and the day before or the day of the surgery. If the hook wire is placed the day before the surgery patients should stay in overnight.

As soon as they are included, patients will fill out a Hospital Anxiety and Depression scale (HAD) questionnaire to determine potential anxiety and depressive disorders.

The included patients will then fill out a satisfaction questionnaire in two steps:during the placement of the device (RFID tag or hook wire),during the postoperative consultation at 1 month

Radiologists and surgeons will fill out a questionnaire dedicated to them, respectively after the localization and surgery procedures.

### Primary and secondary outcomes

The primary outcome is the patient’s satisfaction score with the preoperative localization technique, evaluated by a visual analog scale (see patient questionnaire).

Secondary outcomes are:the patient’s pain score in relation to the preoperative localization technique, evaluated by a visual analog scale (see “patient” questionnaire)the score of the patient’s stress in relation to the preoperative localization technique (see patient questionnaire)the scores of the precision and the operative comfort associated with the device (see surgeons questionnaire)the visualization of the needle on ultrasound, the visualization of the device on ultrasound and on stereotaxic, and the ease of insertion of the device (see radiologists questionnaire)the occurrence or not of a migration of the localization device, the histological data with the presence of the lesion in the surgical specimen, the invasion of the margins and therefore the resulting rate of revision surgery.

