#### Secondary analysis

The secondary analysis consists of the analysis of the global score values, and the comparison between the two study groups, of the patient questionnaires (with matching or adjustment for baseline anxiety values), the surgeons and the radiologists, using the Student’s t-test (/ non-parametric test) or the chi-square test (/ Fisher’s exact test), depending on the nature of the data. If a statistically significant difference between groups is found, a post-hoc analysis will follow on the questionnaire items, with multiple testing corrections.

Data on localization quality will also be analysed and compared between groups using one-tailed tests to ensure that they do not indicate an inferiority of the experimental device.

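### Radiologists' scores are compared between devices without regard to guidance mode; stratifying or adjusting for ultrasound versus stereotaxy would be a cheap improvement to a secondary objective

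*Protocol article*

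**What the plan says.** All references are to the protocol article.

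- **Guidance modes (Background).** The wire procedure is described as "using a hook wire to mark the area of concern under ultrasound or stereotactic localization". The tag, likewise, "can be positioned under ultrasound or stereotactic guidance". The eligibility table does not restrict the mode.
- **Radiologist outcomes (Primary and secondary outcomes).** They are "the visualization of the needle on ultrasound, the visualization of the device on ultrasound and on stereotaxic, and the ease of insertion of the device". Read as four items, three name an imaging mode; only ease of insertion does not.
- **Comparison (Secondary analysis).** The unit is "the analysis of the global score values, and the comparison between the two study groups". It covers the questionnaires of the patients and of "the surgeons and the radiologists, using the Student’s t-test (/ non-parametric test) or the chi-square test (/ Fisher’s exact test").
- **Adjustment (Secondary analysis).** It is attached to one questionnaire and one variable: "of the patient questionnaires (with matching or adjustment for baseline anxiety values"). None is attached to the radiologists' questionnaire.
- **Items (Secondary analysis).** If the groups differ significantly, "a post-hoc analysis will follow on the questionnaire items, with multiple testing corrections".
- **Allocation (Study design; Primary analysis).** Groups are formed by alternating blocks of 20 in time, without randomisation. The propensity score contains HAD anxiety only.
- **Data (Data collections).** Guidance mode is not listed by name; questionnaire responses are.

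**The concern.** Comparing radiologists' perception of the two devices is a stated secondary objective. How well a needle or device is seen, and how easily it goes in, may depend on the imaging used as well as on the device. Nothing in the allocation or the stated analysis balances guidance mode between the groups. The devices are also placed on different occasions (the tag at the senology consultation, the wire close to surgery). That is a possible route to a different mix, although the documents do not say that it affects the choice of guidance.

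If the mix did differ systematically, a device could look better or worse because of how it was guided. The item-level tests would not protect against this, because the global test is their gate. An imbalance could open that gate without a device effect, or keep it closed when there is one.

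**Working it through.** **The plan's own figure.** No sample size is given for the radiologist comparison. The primary one supplies the group size and SD used below. For an effect of 0.75 SD, two-sided 5% and 80% power, the normal approximation gives 2 × (1.960 + 0.842)² / 0.75² = 27.9, so 28 per group. The exact t-test gives 28.9, so 29. The stated 30 agrees closely, and 40 per group are enrolled. This point does not depend on that calculation.

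**Inputs**

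- From the documents: 40 per group. The SD of 1.5 points on a 0–10 scale is stated for patient satisfaction and is borrowed here.
- Assumed, because the documents are silent: the share of ultrasound placements in each group (p₀, p₁), and the gap g in mean score between modes, taken as 1, 2 or 3 points. The borrowed SD is treated as the within-mode SD. Tests are two-sided at 5%.

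**Bias.** With no device effect, the expected difference in group means is (p₁ − p₀) × g. For 70% versus 90% it is 0.2, 0.4 or 0.6 point.

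**Rejection rate.** The table shows how often the unadjusted t-test rejects when there is no device effect (20,000 simulated trials per cell).

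| Ultrasound share, one group vs the other | g = 1 | g = 2 | g = 3 |
|---|---|---|---|
| 70% vs 70% | 5% | 5% | 5% |
| 70% vs 80% | 6% | 8% | 10% |
| 70% vs 90% | 9% | 18% | 28% |
| 60% vs 90% | 14% | 34% | 54% |
| 50% vs 90% | 21% | 55% | 78% |

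With guidance mode as a covariate, the rate is about 4% to 6% in every cell (4,000 trials each).

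**Check by hand, 70% vs 90%, g = 2.** The group variances are 1.5² + 2² × 0.7 × 0.3 = 3.09 and 1.5² + 2² × 0.9 × 0.1 = 2.61. The standard error is √((3.09 + 2.61)/40) = 0.377, and 0.4/0.377 = 1.06. The rejection probability is about P(Z > 1.96 − 1.06) = P(Z > 0.90) = 18%, as simulated.

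**The case against.** The strongest reply is that the questionnaire, in Additional file 1, is not shown. It may have a not-applicable option, a scoring rule or a field for guidance mode, and covariates for a secondary questionnaire are often left to an analysis plan. The outcome list already separates the visualisation items by mode, and corrected item-level tests are foreseen. The documents show no sign of a different mix: one centre, one set of criteria, alternating blocks.

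Much of this stands. It rules out three stronger readings that a reader might infer.

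- **That chance imbalance alone biases the test.** If 30% of placements in both groups were stereotactic, the standard error of the difference in shares would be √(2 × 0.3 × 0.7/40) = 0.10, so gaps of 20 points would arise in about 5% of trials. The t-test's variance already includes this variation, and the first row of the table stays at 5%. Only a systematic difference in mix inflates the error.
- **That the global score is built from different items in different patients.** This is inferred from the item wording. The documents do not say how the score is formed, how an inapplicable item is treated, or that each patient is imaged in only one mode.
- **That only one pooled test is planned.** Item tests follow, though only after a significant difference.

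What the reply does not remove is that the section itself fixes an unadjusted comparison for radiologists while providing adjustment for patients. A not-applicable rule would settle how to score an item, not an unequal mix. Ease of insertion, whose wording names no mode, would remain exposed.

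**Conclusion.** This is a cheap improvement to a secondary objective; the documents do not show an error. The stated comparison leaves out a variable named in three of the four radiologist items, in a design that does not balance it by randomisation. The bias equals the difference in mix times the gap between modes, and is zero if either is zero. Neither is known. Over the assumed ranges, the false-positive rate runs from 5% with an equal mix to 9–28% with 70% versus 90% ultrasound, and higher with larger imbalances; adjustment brings it back to about 5%. These figures rest on the borrowed SD and on assumed shares and gaps, so they show the mechanism and do not predict this trial. The primary conclusion on patient satisfaction does not rest on this comparison.

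**What to change.** In the Secondary analysis section:

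1. Compare ease of insertion and any global radiologist score with guidance mode as a stratum or covariate.
2. Compare each mode-specific visualisation item only among placements done under that mode, in both groups.
3. Record guidance mode for each patient, if the questionnaire does not already capture it.
4. Report the mode split by device beside each radiologist result.

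The cost is at most one recorded field, which the radiologist already knows, and one extra model term. The downside is smaller denominators for the mode-specific items. Adjustment also needs both modes to occur in both groups, which the reported split would show. No extra patients or procedures are needed.

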### RFID Tag

The LOCalizer™ wire-free guidance system is designed by Hologic© to mark and guide to non-palpable breast lesions thanks to a radiofrequency identification (RFID) tag. Each tag has a unique identification number that is displayed on a reader and can be placed in the breast any time prior to or on the day of surgery.

### Questionnaires

We created the questionnaires to evaluate the patients’ satisfaction as well as the practical aspects of the localization technique from the radiologists and surgeons points of view (Additional file 1). Our questionnaires are partly based on validated models such as the Visual Analog Scale; to date, there is no fully standardized and validated model or questionnaire that would allow us to evaluate all the objectives of our study. Patients will also fill out a Hospital Anxiety and Depression scale (HAD) questionnaire [7].

### Patient selection

Inclusion and exclusion criteria are presented in Table 2. Patients over 18 year’s old requiring conservative surgery for an histologically proven non-palpable breast lesion (fibroadenomas, papillomas, atypical lesions and neoplasia) will be included.

**Table 2 Tab2:** Inclusion and non-inclusion criteria

**Inclusion criteria**	• Female over 18 years old • Requiring conservative surgery for an histologically proven non-palpable breast lesion (fibroadenomas, papillomas, atypical lesions and neoplasia) • Speaking and understanding French • Patients referred to senology for localization of non-palpable breast lesions by surgeons • Affiliated to the French Social Security System • Able to give informed consent
**Non-inclusion criteria**	• Multiple breast lesions • Patients with breast neoplasia during pregnancy • Persons deprived of liberty or under guardianship or incapable of giving consent • Refusal to participate

The estimated duration of patients’ enrolment is 1 year and 6 months: 80 patients will be enrolled and followed from the inclusion until one month after surgery. A sequential inclusion in time will be performed: 20 inclusions in the control group (gold-standard) during 3 months, then 20 patients in the “RFID group” for the following 3 months with an interim statistical analysis, before repeating the inclusion scheme. When patients consent to participate in the study, they are informed of the device they will receive. Patients of the hookwire group are convened the day before the surgery to install the device. Patients with the RFID tag have the device installation at least one week before their surgery.

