### Statistical analysis

#### Primary analysis

The main analysis consists of comparing the patient satisfaction scores between the two groups, RFID vs. gold standard, and, if the difference in mean scores is clinically significant (difference of about 20%), to test whether it is statistically significant using Student’s t-test or a non-parametric test depending on the nature of the data. A propensity score matching will be performed beforehand to compensate for the non-randomized design of the study. We will include in the calculation of the propensity score the anxiety measured by the HAD scale at inclusion, the only measurable confounding factor we estimate being related to the primary outcome.

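### HAD anxiety, the only propensity-score variable, is probably recorded when patients already know their device, so matching on it may bias the satisfaction comparison in either direction, by an unknown amount

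*Protocol article*

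**What the plan says.** Four statements in the protocol article bear on this.

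- **Disclosure.** Patient selection: "When patients consent to participate in the study, they are informed of the device they will receive".
- **Timing of the HAD.** Study design: "As soon as they are included, patients will fill out a Hospital Anxiety and Depression scale (HAD) questionnaire". The Abstract (Methods) agrees: "Patients will fill out a Hospital Anxiety and Depression scale (HAD) questionnaire at the time of inclusion".
- **Use of the HAD.** Primary analysis: "A propensity score matching will be performed beforehand to compensate for the non-randomized design of the study". On its content: "We will include in the calculation of the propensity score the anxiety measured by the HAD scale at inclusion", described as "the only measurable confounding factor we estimate being related to the primary outcome". Secondary analysis uses the same score for the patient questionnaires, "with matching or adjustment for baseline anxiety values".
- **Timing of the procedure.** For RFID patients, the Abstract says of the senology consultation: "The RFID tag will be placed during this consultation". Study design puts the wire on the day before surgery or the day itself.

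No section places the HAD before the patient learns her device.

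**The concern.** A propensity score should contain only variables that the exposure, or knowledge of it, cannot have changed. If hearing which device she will receive alters a woman's anxiety, the HAD score is no longer a clean baseline. Matching wire and RFID patients to equal HAD anxiety then compares women who would have differed in anxiety before they were told.

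The article supplies a reason to expect this. The Abstract and Background describe the wire as painful, stressful and a source of anxiety, and stress related to the technique is a secondary outcome. If wire patients become more anxious on being told, matching removes part of any advantage of RFID. A second mechanism works the other way: an RFID patient may answer with her procedure imminent, while a wire patient's is still ahead. That could raise anxiety in the RFID arm and push the matched estimate in favour of RFID.

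At stake is the primary comparison, because HAD anxiety is the only covariate named for its adjustment. The secondary patient comparisons share the problem.

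**Working it through.** **Order of events.** Disclosure is tied to consent (Patient selection). The HAD is tied to inclusion, or to the moment just after it (Abstract, Study design). Inclusion requires consent, so the HAD comes after disclosure or, at the earliest, together with it. This is an inference from separate sections; no single sentence states it.

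**The plan's own figure.** Inputs from Sample size calculation: effect size 0.75 SD, SD about 1.5 points, power 80%, type I error 5%. The article does not state one- or two-sided; two-sided is taken here.

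n per group = 2 × (1.960 + 0.842)² / 0.75² = 27.9, so 28. The exact t-test calculation gives 29, and power at 30 per group is 81.5%. The stated 30 reproduces, so this point does not touch the sample size arithmetic.

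**Bias from matching on a shifted score.** Let *s* be the between-arm shift in HAD anxiety (in SD) caused by disclosure or timing, and *r* the strength of the inverse correlation between anxiety and satisfaction. If RFID patients score *s* lower, two patients matched on HAD differ by *s* in underlying anxiety, and the matched comparison estimates

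matched effect = true effect − *r* × *s*.

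If RFID patients score *s* higher, the sign reverses. **Neither *s* nor *r* is in the document; the values below are assumptions.** The simulation starts from 40 per group, loses 10% at random and applies 1:1 nearest-neighbour matching with a caliper of 0.2 SD.

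| *s* | *r* | Bias (SD) | Matched effect (SD) | In points (× 1.5) | Power, 30 per group | Simulated matched effect (SD) |
|---|---|---|---|---|---|---|
| 0 | 0.3 or 0.5 | 0 | 0.75 | 1.125 | 81.5% | 0.75, 0.76 |
| 0.2 | 0.3 | 0.06 | 0.69 | 1.035 | 74.8% | 0.69 |
| 0.2 | 0.5 | 0.10 | 0.65 | 0.975 | 69.7% | 0.64 |
| 0.3 | 0.4 | 0.12 | 0.63 | 0.945 | 67.0% | not run |
| 0.5 | 0.3 | 0.15 | 0.60 | 0.900 | 62.8% | 0.60 |
| 0.5 | 0.5 | 0.25 | 0.50 | 0.750 | 47.8% | 0.51 |

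The largest bias is 0.25 / 0.75 = 33% of the planned effect. In the opposite direction, the same inputs would inflate a true 0.75 SD to 0.75 + 0.25 = 1.00 SD. With no true effect, the simulated two-sided rejection rate was 3.5% to 5.5% at *s* = 0 and 10.3% at *s* = 0.5, *r* = 0.5.

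Loss of matches is negligible in this range: about 26 pairs at *s* = 0 and about 25 at *s* = 0.5.

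**Which patients a change now would reach.** Trial status reports 64 recruited. The scheme is 20 wire, 20 RFID, 20 wire, 20 RFID. If it was followed, 60 patients fill the first three blocks and 4 are in the last, so all 80 − 64 = 16 remaining patients are RFID.

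**The case against.** Four objections carry weight.

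1. **The order is inferred.** A reader might take the article to state that the HAD follows disclosure. It does not. Both steps may fall in one consultation, and an article may leave their exact sequence to the full protocol, which is not shown. This limits the point to probably. It does not remove it, because nothing in the article puts the HAD first and its wording points the other way.

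2. **The size is assumed.** With no shift there is no bias. The HAD is used here to detect anxiety and depressive disorders, while technique-related stress is a separate outcome, so naming the device may move the HAD little. The two mechanisms also oppose each other and may partly cancel. The timing mechanism is the weaker: either the surgeon or the radiologist may offer participation, so the interval from inclusion to placement is not fixed. All of this stands, and it is why the range must start at zero.

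3. **Matching is not the only protection.** A reader might infer that the trial's sole safeguard against non-randomised allocation has failed. The device is set by alternating calendar blocks, not by clinician choice or patient characteristics, and that is itself some protection. The HAD is also meant to be completed before placement, so the issue is anticipation, not experience of the device.

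4. **Reordering now would do harm.** It is tempting to move the HAD before disclosure for everyone still to be enrolled. If the block scheme was followed, that would leave 40 wire and 24 RFID patients measured after disclosure and 16 RFID patients before it. The timing of the matching variable would then differ by arm, which is a fault of the same kind. This objection stands in full and shapes the fix.

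**Conclusion.** The point holds in a limited form. As the article reads, the one variable used for matching is probably collected when the device is already known, and it may partly reflect that knowledge. The matched difference in satisfaction may then be biased in either direction.

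Under an assumed shift of 0 to 0.5 SD and correlation of 0.3 to 0.5, the bias is 0 to 0.25 SD (0 to 0.375 points at an SD of 1.5). If towards the null, power at 30 per group is between about 81% and 48%. The 48% is the edge of an assumed range, with a net shift all in one direction; the document does not support reading it as the expected power. Nor does it support saying that the primary analysis is invalid. What it supports is that the plan should show whether the result depends on this covariate.

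**What to change.** Keep the HAD-matched comparison as the primary analysis and add, before the final analysis:

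- a table of HAD anxiety at inclusion by arm;
- a sensitivity analysis of the primary comparison without HAD matching;
- a sensitivity analysis using covariates that Data collections already lists and that disclosure cannot change: age, pathology and lesion size;
- a statement that the conclusion will be qualified if these disagree with the matched result.

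The plan should also state the order of consent, disclosure and HAD as actually practised.

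Have the HAD completed before the device is named only in complete new wire/RFID block pairs, for example if the sample size re-estimation adds patients. Do not change the order in the last RFID block alone.

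**Cost.** One or two extra analyses on data already collected. The unmatched result is a check on robustness, not a correction, because dropping HAD reopens any confounding by anxiety that was present before disclosure. Any reordering in new blocks separates disclosure from consent, so it would mean changing the consent procedure of an ethics-approved protocol.
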